### 2.10. Patient and Public Involvement

Neither the patient nor the public is involved in the conception, design, or execution of the study. However, participants will be informed about the outcome of the trial via one-to-one consultation and email upon trial completion.

### 2.11. Data Monitoring

The research team will monitor the data internally and have weekly meetings to discuss the progress of the trial and data collection. There is no external data monitoring board. Each participant will be assigned a unique identifier code to be entered in the database. Only patient codes will be entered into the database to ensure the anonymity of the participants. The data will only be entered and accessed by members of the research team. The database will be password protected and encrypted. Missing data will be identified and mentioned with reason. Data obtained throughout the trial will be stored for a duration of 15 years. Handling of personal data will be carried out in compliance with the Malaysia Personal Data Protection Act (PDPA) 2010.

### 2.12. Ethics and Dissemination

This study has obtained human ethics approval from the Human Research Ethics Committee UKM (JEP-2019-566). We have also registered this study protocol at the Thai Clinical Trials Registry (Medical Research Foundation, Bangkok, Thailand; TCTR ID: TCTR20210921004). Any amendments to the protocol will be submitted to the ethics committee for review and will be conveyed to all relevant parties. Written consent (Online Supplementary File 1) will be obtained from all participants before the commencement of the study. Each participant will be assigned a unique identifier to be used in the database. The personal identity of all participants will not be used for any public purpose or for publication, nor will it be accessible to personnel outside of the research team. Results from this study will be disseminated via peer-reviewed publications and presented at relevant international conferences.

## 3. Impact of COVID 19 on Data Collection

### Preliminary Result

The study is currently in the recruitment and initial intervention phase. A total of 5185 patients were screened between September 2020 to May 2021 from digital medical records. A total of 136 participants were identified to be recruited. The intervention process has not yet been started. The overall distribution of participants identified by gender, age, and race is shown in Table 4 below. The overall mean age (±SD) of the participants is 54.9 ± 9.3 years. Among them, there are 81 males and 55 females with predominantly 63.97% Malay, 18.38% Chinese, 15.44% Indian, and 0.02% others. Overall, HbA1c levels of the participants averaged 8.5 ± 1.0%, while fasting plasma glucose levels averaged 8.6 ± 2.5 mmol/L.

## 4. Discussion

The global epidemic of obesity and associated T2DM direly needs a greater emphasis on effective lifestyle intervention programs for patients. Meal replacement is often included as a part of the lifestyle intervention program as it is effective as an initial phase for diabetic patients to lose weight in a therapeutic program [46]. Previous trials utilising meal replacements on obese or T2DM patients have demonstrated significant improvements in HbA1c, weight, lipid profile, insulin sensitivity, and cardiovascular risk factors [47,48,49,50,51].

This prospective, randomised, controlled open-label trial will focus on evaluating the effectiveness of a diabetes-specific meal replacement formulation on the weight loss and glycemic control of obese and overweight T2DM patients. To date, this is the first trial of its kind to test the efficacy of this low glycemic indexed meal replacement formulation containing cinnamon extract (*Cinnulin MS*) on overweight or obese T2DM patients. There is also a lack of studies on short-term meal replacement intervention in a sufficiently powered and well-designed clinical trial in Malaysia. We hypothesised that the meal replacement intervention would be effective in maintaining weight loss, improving glycaemic control parameters, and improving the quality of life of the participants.

Apart from anthropometry and biochemical analysis, a cost-effectiveness analysis of the meal replacement intervention will also be conducted, in comparison with the standard care in public. It is anticipated that this meal replacement intervention in T2DM management would be more cost-effective, as simulated in the other study (Stephen 2010).

Meal replacements have been proven to improve patients’ weight and glycaemic control. However, due to the lack of further intervention following the completion of the initial intervention, it has also been shown to be less effective in maintaining glycaemic control in some meal replacement studies. This is shown in a study by Ash et al., in which the HbA1c levels of the participants who received a 12-week diet intervention with meal replacement returned to baseline levels after their 18th month follow-up [16]. Similar results of weight and HbA1c levels rebounding have been reported in other studies [52,53,54].

The sustainability of the meal replacement formulation to maintain the effect of weight reduction and glycemic control will be assessed by the end of this study through constant monitoring of the participants for another 36 weeks. Possible adverse effects among the participants in the meal replacement trial that we anticipate may occur are nausea or hypoglycemia. The participants will be advised to report any episodes of adverse effects directly to the medical doctor in the research team immediately.

Nevertheless, the commencement of this clinical trial has met with unprecedented challenges due to the COVID-19 pandemic. Most resources and policies have shifted to focus on the management and prevention of the pandemic in the country. As a result, our research progress has been confronted with various restrictions and delays. COVID-19 has led to a restriction of patient visits to clinics for non-essential purposes. Hence, the recruited participants for our study are not permitted to visit the clinic for baseline measurement and intervention.

The European Medicines Association and the US Food and Drug Administration have come out with a series of guidelines and suggestions on conducting clinical trials during the pandemic for better patient protection and to enable continuous trial execution without compromising good clinical practice standards [55,56]. Doherty et al. [57] have reported that one important consensus in handling clinical trials during COVID-19 is reducing the potential COVID-19 exposure risk to patients by minimising hospital visits. Dorsey et al. [57] have suggested that COVID-19 has led to the rise of decentralised studies in which studies may be designed as site-agonistic and flexible in location. Taking the guidelines and approaches from other trials as a reference, we have proposed and outlined a hybrid method for an intervention session that comprises both virtual and physical sessions to mitigate the impact of the delay in the intervention progress [55,56,57,58,59].

One of these methods is to utilise telecommunication software to conduct the diet education online for digitally literate participants. Based on a survey by the American Society of Clinical Oncology on clinical trial participants, nearly all of their respondents (90.3%) indicated telehealth as a potential alternative for conducting clinical trials during the pandemic [60]. Step-by step instructions will be provided to the participants on utilising the online meeting software for conducting diet education. Patient reviews of compliance to meal replacement and adverse events can also be monitored through telecommunications methods such as email, phone, or messaging applications. A study by Aravindhan et al. [61] has reported that virtual interviews for older research participants, because of lockdown measures, are feasible in the current pandemic situation to minimise physical sessions.

Home visits will also be carried out for patients who are unwilling to attend the site for intervention. The phlebotomist and a researcher will visit the patient’s house for blood taking, assisting in the completion of questionnaires and providing instructions on the trial. Strict standard operating procedures will be adhered to in order to ensure the safety of the trial participants and the researchers from COVID-19. This is as suggested by the FDA, who states that consideration should be given for alternative locations for visitations if a patient is not able to go to the investigational site [55]. The investigational product, which is the meal replacement powder, will also be delivered to the participants’ homes [62].

Another possible challenge that we expect to face in this study is maintaining the compliance of the participants who undergo the meal replacement intervention. Although there is no consensus on the acceptable minimum adherence level in clinical trials, it is important to maintain a high level of adherence, as low adherence can lead to a negative impact on the result interpretation and statistical power [63,64]. Mogre et al. reported a middle diet adherence rate of 58.1% for diabetes patients in middle- and low-income countries [65]. An adherence rate between 43% and 78% of participants receiving treatment during a clinical trial for chronic conditions can be classified as being compliant [66]. To minimise the risk of a high dropout rate, the participants will be monitored closely via phone contact, video call, and Whatsapp messages. Daily reminders will be sent to remind the participants of adhering to the meal replacement routine. Participants will be given flexibility in choosing which days they prefer to consume the meal replacement on as long as they choose 5 days a week.

### 4.1. Limitation

The major limitation of this trial is that it is a single-centred study. Hence, the generalisability of the study might be limited to the Malaysian T2DM population who visit the public health sector to seek treatment. Meal replacement products are also given to the participants without any charge. This might also impact the generalisability of the study, as dropout rates for less motivated patients in real-world settings in such intervention programs are likely to be higher. To reduce this limitation from the generalisability perspective, we have used randomisation techniques during sampling to maximise the representation of our target population.

Due to the nature of the study, the treatment allocation will not be blinded to both participants and the researchers. However, to minimise selection bias, randomisation into groups and statistical analysis will be carried out by a third-party statistician.

The taste and texture of the meal replacement we are studying might also affect the compliance of the participants, as there are reports from testers who dislike the cinnamon taste of the liquid meal replacement. We will inform our study participants beforehand to get them to gradually adapt to the taste.

### 4.2. Implication and Future Implementation

The recruitment: intervention and follow-up process will have approximately a 2-year delay as a result of the COVID-19 pandemic. We expect the results to be available and publishable by June 2023. This study will enable us to assess the potential of this low glycaemic indexed meal replacement and will allow for it to be included as a part of lifestyle intervention and implemented into present healthcare programs. This research can also help in assessing the sustainability of meal replacements upon the secession of the intervention. Future research can be carried out to develop a lifestyle intervention module incorporating a short-term meal replacement therapy for the maintenance of T2DM patients.

## Figures and Tables

**Figure 1 ijerph-19-04188-f001:**
[figure not shown]
Research Flow Chart.

**Table 1 ijerph-19-04188-t001:** Inclusion and Exclusion Criteria.

Inclusion Criteria	Exclusion Criteria
Aged 20–65 years old	On insulin treatment
Diagnosed with T2DM for at least 6 months with baseline HbA1c levels between 7.5% and 12% for the past 3 months	With chronic kidney disease or on continuous ambulatory peritoneal dialysis or hemodialysis (GFR < 30 mL/min/1.73 m^2^)
Overweight or obese with BMI ≥ 25 kg/m^2^	With hepatic diseases (ALT > 120 IU/L)
On stable doses of any oral hypoglycaemic agents for the past 3 months	With history of chronic alcohol abuse
	Pregnant and lactating women
	Currently consuming any weight reduction products or any slimming prescriptions
	Currently involving in weight loss programs
	Record of COVID-19 diagnosis

**Table 2 ijerph-19-04188-t002:** Protocol for calculation in G*Power.

Sample Size Calculation	
F tests—ANOVA: Repeated measures, between factors	
Analysis: A priori: Compute required sample size	

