#### 1.1.1. Primary Endpoint

Changes in HbA1c and bodyweight from the beginning of treatment to week 12 after initiation of treatment

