### 2.2. Sample Size

Sample size is calculated using G *Power 3.1 software. The protocol for calculation is as shown below in Table 2. We employed an effect size of 0.2055067, which is obtained from the mean difference value of the HbA1c (%) result in a study by Keogh and Clifton [18]. Based on the calculation, a total of 120 participants is needed for the study. In order to account for up to a 30% dropout, a total of 156 participants will be recruited for this study.

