#### 2.8.7. Metabolic Profiles

Blood samples of the participants will be collected by a qualified phlebotomist at baseline, on the 12th week and the 48th week. Prior to the day of blood collection, participants will be reminded to fast for eight hours (only plain water is permitted). After that, a total of 7.5 mL of venous blood sample will be taken for biochemical analysis. Blood will be transferred into their respective types of vacutainers and delivered to a certified diagnostic laboratory (Lablink (M) Sdn Bhd, Kuala Lumpur, Malaysia; MS-ISO 15189) for analysis. The results of the blood test will be mailed or given to the participants during the next follow-up. Contact details are provided along with the results to enable the participants to contact the investigators or physician if they have any inquiries. The biochemical parameters measured are listed below:

aHbA1c

Blood samples will be collected in an EDTA tube and measured using an automated high-performance liquid chromatography analyser Adams A1c HA-8180V (Arkray, Tokyo, Japan).

bFasting Blood Glucose

Blood samples will be collected in a sodium fluoride tube and measured using an automated photometric analyser ARCHITECT c16000 and c8000 (Abbott Laboratories, North Chicago, IL, USA).

cFasting Insulin Level

Blood samples will be collected in a serum separator tube, and the fasting insulin level is measured using an automated chemiluminescent analyser (Advia Centaur XP Immunoassay System, Siemens, USA). Insulin resistance index (HOMA-IR) is calculated according to the formula: fasting insulin (micro U/L) × fasting glucose (nmol/L)/22.5 [36].

dLipid Profile Test

Total cholesterol, HDL cholesterol, LDL cholesterol, and total glycerides will be analysed. Blood samples will be collected in a plain tube and measured using an automated photometric analyser ARCHITECT c16000 and c8000 (Abbott Laboratories, USA).

eLiver Profile Test

Total protein, albumin, bilirubin total, Alkaline Phosphatase (ALP), and Alanine Amino Transferase (AST) will be analysed. Blood samples will be collected in a plain tube and measured using an automated photometric analyser ARCHITECT c16000 and c8000 (Abbott Laboratories, USA).

fRenal Profile Test

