### 2.9. Statistical Analysis

Statistical Package for the Social Sciences (SPSS) program version 23.0 will be used to analyse the data. The data will be presented as mean ± SD for parametric data and median (range) for non-parametric data. The normality of data distribution will be tested using the Shapiro–Wilk test. A *p*-value of <0.05 will be used to denote statistical significance. Descriptive analysis including frequencies, percentage, mean, and standard deviation will be used to analyse sociodemographic data and blood pressure.

For the effects of meal replacement on metabolic profiles, anthropometric measurements, satiety levels, hormonal changes, and QoL scores, mixed-design ANOVA will be used to compare between the intervention group and the control group to determine the interaction effect of intervention and time.

To determine the cost-effectiveness, incremental cost-effectiveness ratios (ICER) will be calculated by dividing the difference in total costs (between control and treatment) with the difference in the chosen measure of health outcome or effect (QALY). To assess the sustainability of the meal replacement, mixed-design ANOVA will be used to compare clinical parameters and hormonal level changes between groups on week 12 and week 48.

The main analysis will be conducted in the intention-to-treat (ITT) population in which missing values will be predicted by using the estimating equation method by adapting statistical models to the data observed using the missing-at-random method. Complete case analysis will also be performed in the per-protocol (PP) population.

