**Input**	
Effect size f	= 0.2055067
α err prob	= 0.05
Power (1-β err prob)	= 0.80
Number of groups	= 2
Number of measurements	= 4
Corr among rep measures	= 0.5

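### Table 2 powers a between-groups main effect over four measurements, but the primary question is the week-12 change tested by group-by-time interaction; on the plan's own inputs that test has about 61% power at 120, not 80%.

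*Protocol article*

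**What the plan says.** - **Primary endpoint (section 1.1.1):** "Changes in HbA1c and bodyweight from the beginning of treatment to week 12 after initiation of treatment".
- **Planned test (section 2.9):** for metabolic profiles, anthropometry and other outcomes, "mixed-design ANOVA will be used to compare between the intervention group and the control group to determine the interaction effect of intervention and time".
- **Sample size (section 2.2 and Table 2):** the routine is "F tests—ANOVA: Repeated measures, between factors". The text says "We employed an effect size of 0.2055067", and that this was "obtained from the mean difference value of the HbA1c (%) result" of an earlier study. No means, SD or scale are given. The other inputs are alpha 0.05, target power 0.80, two groups, four for "Number of measurements" and correlation 0.5. The output is 120 in total with actual power 0.8063. Section 2.2 then recruits 156 to allow for up to 30% dropout.
- **HbA1c schedule (section 2.8.7):** "Blood samples of the participants will be collected by a qualified phlebotomist at baseline, on the 12th week and the 48th week". Table 3 agrees, with HbA1c marked at weeks 0, 12 and 48 only. Section 2.1, however, describes outcome assessment at baseline, week 6 and week 12, then the same parameters at week 48. That makes four visits.

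**The concern.** The between-factors routine tests whether the groups differ in each patient's mean over all visits. This is not the question posed in sections 1.1.1 and 2.9, for three reasons.

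1. It takes credit for averaging four values, whereas the week-12 change uses two.
2. It treats the assumed difference as the average over every measurement. If baseline is one of them, randomisation gives no expected difference there. And if the same difference were present at every visit, the interaction test would have nothing to detect.
3. It responds to correlation in the opposite direction. A higher correlation lowers the power of the averaged comparison and raises the power for change.

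The printed 80% therefore does not describe the primary test. A reader could take a null HbA1c result as coming from a trial with 80% power for that question, when the plan's own inputs do not show this.

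**Working it through.** **Inputs.** From section 2.2 and Table 2: f = 0.2055067, m = 4, ρ = 0.5, α = 0.05, N = 120. For two equal groups d = 2f = 0.411. From section 2.2: 156 recruited, and 156 × 0.7 = 109.2, so about 109 remain after 30% dropout.

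**Step 1. Reproduce Table 2.**
λ = f²·N·m / (1 + (m − 1)ρ) = 0.2055067² × 120 × 4 / 2.5 = 8.1087. The critical F(1, 118) is 3.9215 and the power is 0.8063. All three match, so the powered test is identified without doubt. With m = 3, the number of HbA1c draws in Table 3, the same formula gives 0.781, and 126 patients are needed for 80%.

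**Step 2. Power for the week-12 change** (group-by-time over weeks 0 and 12, equivalent to a two-sample t test on change). Reading 0.411 as raw SDs:
SD of change = SD × √(2(1 − ρ)), which equals 1.0 SD at ρ = 0.5.
Noncentrality at N = 120 is 0.411 × √(120/4) = 2.25 on 118 df, giving power 0.608.

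| Evaluable | ρ = 0.3 | ρ = 0.5 | ρ = 0.7 |
|---|---|---|---|
| 109 | 0.44 | 0.57 | 0.78 |
| 120 | 0.47 | 0.61 | 0.82 |
| 156 (no dropout) | 0.58 | 0.72 | 0.91 |

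At ρ = 0.5, 80% power needs 188 evaluable. If 0.411 is instead in SDs of change, the ρ = 0.5 column applies whatever the correlation. The difference detectable with 80% power at 120 is about 0.52 SD of change.

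**Step 3. Interaction over all three HbA1c visits.** Here λ = (N/4) Σ(δₜ − δ̄)² / (1 − ρ), with 2 and 236 df. At N = 120 and ρ = 0.5, with 0.411 SD at week 12:
- full effect kept at week 48: 0.63
- half kept at week 48: 0.50
- none kept at week 48: 0.63

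**Step 4. Table 2's own test under randomisation.** With no difference at baseline and 0.411 SD at both later HbA1c visits, the averaged difference is 0.411 × 2/3 = 0.274 SD. The main-effect test then has power 0.45.

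**Step 5. Baseline-adjusted ANCOVA at week 12, for comparison only.** Residual SD = SD × √(1 − ρ²) = 0.866 SD at ρ = 0.5. Power is 0.73 at 120, 0.69 at 109 and 0.84 at 156, and 142 are needed for 80%. The detectable difference at 120 is 0.516 × 0.866 = 0.447 SD. Section 2.9 does not plan this analysis.

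**The case against.** **The scale of f is unknown.** This stands. The HbA1c difference and SD behind it are not shown, so the size of the shortfall is conditional. In raw SDs, the change test reaches 80% at 120 once the correlation is about 0.68 or more. But the plan states 0.5, and at 0.7 Table 2's own power would fall to 0.72. No single correlation supports both the printed figure and the planned test.

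**156 are recruited, and the main analysis is intention-to-treat with missing data modelled.** This is why a range of N is shown. At ρ = 0.5 the change test stays below 80% even with nobody lost (0.72).

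**Four measurements may be a deliberate count.** Section 2.1 does imply four outcome visits, so the entry cannot simply be called an error. It conflicts with section 2.8.7 and Table 3, and the documents must be reconciled.

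**G*Power's interaction option gives a smaller N for the same f** (50 for two time points). In that option f is a different quantity. With two time points and ρ = 0.5 it implies a difference in change of 4f = 0.82 SD, twice what Table 2 encodes.

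**Stronger readings.** A reader might infer that Table 2 is miscalculated; it reproduces exactly. A reader might also infer that power is 61% without qualification, or that the trial must be enlarged. The first depends on f and ρ as above. The second does not follow, because an honest restatement at the planned size is enough. Nor may 73% be quoted as the trial's power while section 2.9 plans an interaction test.

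**Conclusion.** The mismatch is certain from the text: the powered test, the primary endpoint and the planned analysis do not correspond, and the number of measurements conflicts with the HbA1c schedule. Its size is conditional. With f read as 0.411 raw SD and the plan's correlation of 0.5, power for the week-12 HbA1c change is about 61% at 120 evaluable, so the stated 80% is not delivered on the plan's own inputs. It would be delivered at 120 only under a correlation that the plan does not assume. The calculation covers HbA1c alone. Body weight, the other primary endpoint, has no power figure in section 2.2, and the documents give no effect size from which to derive one.

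**What to change.** 1. State in section 2.2 the HbA1c mean difference and SD behind f, and whether the SD is of raw values or of change.
2. Replace Table 2 with a calculation for the week-12 change (group-by-time over weeks 0 and 12). Restate the power (about 61% at 120 on present inputs) or the difference detectable with 80% power (about 0.52 SD of change), and show the range over correlation and over 109 to 156 evaluable.
3. As an alternative to item 2, amend section 2.9 so that the primary analysis is week-12 ANCOVA adjusted for baseline, and size for that: about 73% at 120, detectable difference about 0.45 SD, both at correlation 0.5. These figures may be used only if section 2.9 changes too.
4. Give the corresponding figure, or an explicit statement, for body weight.
5. Reconcile the HbA1c visits in section 2.1 with section 2.8.7 and Table 3.

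The cost is rewording sections 2.1 and 2.2 and Table 2 (and section 2.9 under the alternative), and a less favourable stated power. No added patients are required. The article's preliminary-result section says the intervention had not started, so the change can precede any outcome data.
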